### Data collection

2.3

Baseline data collection: Eligible children will be offered to participate in the study during a programmed visit in a pre-travel health clinic or in a PCC. In the first visit, the parents or legal guardians will be interviewed to complete a questionnaire including socio-demographic, epidemiological, and clinical data. A tuberculin skin test (TST) will be performed and read 48 to 72 hours later. Figure 2 shows the study flowchart.

**Figure 2 F2:**
[figure not shown]
Timeline of study visits and procedures.

The TST will be made within 30 days prior to the trip. In BCG vaccinated children, TST will be performed and if the result is positive, a *QuantiFERON-Plus©* (QFT-Plus) test will be carried out to confirm the infection. Subsequently, if the QFT-Plus test is positive, the child will be excluded from the study and treated for LTBI.

Follow-up: A visit will be scheduled 8 to 12 weeks after returning from the trip. Here, a questionnaire with epidemiological and clinical data about the trip will be completed and a TST and QFT-Plus test will be simultaneously performed.

Children diagnosed with LTBI or TB, either at baseline or at follow-up, will receive treatment as per national guidelines, and relatives will be referred for contact tracing. Similarly, the investigators will verify the need for other preventive measures (malaria chemoprophylaxis, helminthiasis study, other immunizations, etc).

Data registration: The information collected in the questionnaires will be registered and managed in REDCap (Research Electronic Data Capture) tools hosted at Fundació de Docència I Recerca Mútua Terrassa. REDCap is a secure, web-based software platform designed to support data capture for research studies.^[21,22]^

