**Methods and analysis::**

A prospective study will be carried out in collaboration with 21 primary health care centres (PCC) and 5 hospitals in Catalonia, Spain. The study participants are children under 15 years of age, either immigrant themselves or born to immigrant parents, who travel to countries with high incidence of TB (≥ 40 cases/100,000 inhabitants). A sample size of 492 children was calculated. Participants will be recruited before traveling, either during a visit to a travel clinic or to their PCC, where a questionnaire including sociodemographic, epidemiological and clinical data will be completed, and a tuberculin skin test (TST) will be performed and read after 48 to 72 hours; patients with a positive TST at baseline will be excluded. A visit will be scheduled eight to twelve-weeks after their return to perform a TST and a QuantiFERON-TB Gold Plus test. The incidence rate of LTBI will be estimated per individual/month and person/year per country visited, and also by age-group.

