#### Primary outcome

2.4.1

The primary outcome is the diagnosis of LTBI and/or TB after travelling to a high TB incidence country in accordance with World Health Organization (WHO) guidelines.^[1]^ At the end of the study, patients will be classified as: “not infected; LTBI/TB disease; unknown/lost to follow-up”. Table 2 shows study variables and timing of data collection.

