### TST and QFT-Plus test procedures

2.5

Tuberculin Skin Test (TST): TST will be performed by intradermal injection of 2 UT of PPD RT23 (Statens Serum Institut, Copenhagen, Denmark) and read after 48 to 72 hours. A positive test is defined as an induration greater than or equal to 10 mm according to recommendations from the *Agència de Salut Pública de Catalunya*^[23]^ and WHO guidelines.^[1]^

QuantiFERON-TB Plus (QFT-Plus) (Cellestis, Victoria, Australia; QIAGEN, Dusseldorf, Germany): We will draw four ml of blood per child and interpret the QFT-Plus test according to manufacturer's instructions. Values ≥ 0.35 IU/ml in either TB1 and/or TB2 antigen tubes will be considered positive.^[24]^ In the case of QFT-Plus values ≥0.2 and <0.35 (gray zone), the test will be repeated 4 to 8 weeks later. QFT-Plus can have a positive, negative or indeterminate result.

If TST and QFT-Plus results are discordant, the test with a negative result will be repeated 4 to 8 weeks later.

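### Infection is ruled out before travel by TST alone but looked for afterwards by TST and QFT-Plus, so a child with only a positive QFT-Plus could be counted as travel-acquired although the timing is unknown

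*Protocol article*

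**What the plan says.** Section 2.3 (Data collection) sets the baseline test for all children: "A tuberculin skin test (TST) will be performed and read 48 to 72 hours later". QFT-Plus enters at baseline by one route only. The text under Figure 2 begins "In BCG vaccinated children, TST will be performed and if the result is positive, a" and goes on to a confirmatory QFT-Plus; then, "if the QFT-Plus test is positive, the child will be excluded from the study and treated for LTBI". The abstract has no such step and says that "patients with a positive TST at baseline will be excluded".

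At follow-up, 8 to 12 weeks after return, the schedule is different: "a TST and QFT-Plus test will be simultaneously performed".

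Section 2.4.1 defines the endpoint: "The primary outcome is the diagnosis of LTBI and/or TB after travelling to a high TB incidence country", in line with WHO guidelines. Children end in one of three classes: not infected, LTBI/TB disease, or unknown/lost. Section 2.6 turns the diagnoses into a rate per month and per person-year, and section 2.2 takes the initial proportion as 0%.

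Section 2.5 sets QFT-Plus positivity at 0.35 IU/ml or more and, for disagreement, states: "If TST and QFT-Plus results are discordant, the test with a negative result will be repeated 4 to 8 weeks later". It does not say how a child is classed if the two tests still disagree.

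**The concern.** An incidence rate needs the same state to be excluded at the start as is detected at the end. Here the starting 0% is established by one assay and the final proportion by two. Every child who enters with a negative TST does so without a QFT-Plus. If that child is QFT-Plus-positive and TST-negative after travel, the data cannot separate three explanations: infection on the trip, infection before it that the baseline TST missed, and a false-positive QFT-Plus.

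Earlier infection is plausible, because the Introduction describes a higher TB burden in immigrant families and section 2.1.2 excludes only previous TB or LTBI. The same cases feed both objectives, the incidence rate and the risk-factor regression. With about eight events expected, a few misdated cases would matter to both.

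**Working it through.** **1. The schedule side by side.**

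| Child at entry | Tests before travel | Tests after travel |
|---|---|---|
| TST-negative | TST | TST + QFT-Plus |
| BCG-vaccinated, TST-positive, QFT-Plus not positive (section 2.3) | TST + QFT-Plus | TST + QFT-Plus |

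Only the second row has a baseline QFT-Plus. Under the abstract's wording that row is empty, so the abstract and section 2.3 need to be reconciled.

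**2. Whether the repeat rules help.** Section 2.5 repeats the negative member of a discordant pair, and repeats QFT-Plus values from 0.2 to below 0.35, which are also under the positivity cut-off. A positive QFT-Plus is never rechecked. Both repeats follow the trip, so neither shows QFT-Plus status before it.

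**3. The plan's own figure.** Inputs from section 2.2: two-sided alpha 0.05, power 80%, 0% to 2%, dropout 20%. For paired proportions with discordant cells 0.02 and 0:

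n = (1.960 + 0.842)² × 0.02 / 0.02² = 7.849 / 0.02 = 392.4, so 393; 393 / 0.8 = 491.25, so 492.

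The stated 492 is reproduced. Evaluable children: 492 × 0.8 = 393.6, about 394. Expected true events: 394 × 0.02 = 7.9.

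**4. Size of the possible artefact.** Let q be the share of retained children already TST-negative/QFT-Plus-positive before travel, from old infection or false positivity. The documents give no value; 0.25% to 2% is assumed. Suppose the pattern persists and is classed as LTBI.

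- Extra cases = 394 × q.
- Observed proportion = 0.02 + 0.98q (the 2% truly infected are not counted twice).
- Artefact share of counted cases = 0.98q / (0.02 + 0.98q).
- With no reversions, six conversions give exact McNemar p = 2 × 0.5⁶ = 0.031; five give 0.0625. The last column is the binomial chance of six or more carried-over cases if nobody is infected on the trip.

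| q (assumed) | Extra cases | Observed proportion | Artefact share | P(≥6), no travel infection |
|---|---|---|---|---|
| 0.25% | 1.0 | 2.25% | 11% | <0.001 |
| 0.5% | 2.0 | 2.49% | 20% | 0.015 |
| 1% | 3.9 | 2.98% | 33% | 0.20 |
| 2% | 7.9 | 3.96% | 49% | 0.80 |

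**5. Would requiring both tests positive solve it?** Assume 5% pre-existing LTBI, 80% sensitivity for each test and independent errors (none of these is in the documents).

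- Missed at baseline: 0.05 × 0.2 / (0.05 × 0.2 + 0.95) = 1.04% of TST-negative entrants, or 4.1 of 394.
- QFT-Plus-positive after travel: 4.1 × 0.8 = 3.3.
- Positive on both: 3.3 × 0.8 = 2.6. These would still be called new.
- True events retained: 7.9 × 0.8 × 0.8 = 5.0. The binomial chance of six or more events falls from 80% to 39%.

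**The case against.** The strongest objection is that nothing in the article makes isolated QFT-Plus positivity a case. Diagnosis is deferred to WHO guidelines, persistent discordance is left unclassified, and the full protocol may contain the rule. This stands, and it makes the point conditional. A reader might infer that the plan does count these children as incident; the text does not support that. If a case needed both tests positive, isolated QFT-Plus results would drop out and the bias would be much smaller.

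Second, for a child with a negative baseline TST, a positive TST after travel is a conversion. This also stands. Only the TST-negative/QFT-Plus-positive group is affected, not the outcome as a whole.

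Third, the Discussion concedes that discordant results can hamper the calculation of incidence rates and calls this universal. That covers imperfect tests. It does not cover testing with one assay before and two after, which is a choice of this design and is not mentioned.

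Fourth, q is assumed, and the sensitivity-based figures also assume independent errors. If children missed by TST also tend to be missed by QFT-Plus, the 3.3 is too high. It is tempting to say that the artefact is as large as the signal, but that holds only at the top of the assumed range.

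**Conclusion.** The asymmetry is plain from the article and no stated rule removes it. Children who are TST-negative/QFT-Plus-positive after travel without a baseline QFT-Plus have infection of unknown timing at best, and the three final classes have no place for them. If they are classed as LTBI, the rate attributed to the trip is biased upward: by about 1 to 8 cases on top of about 8, or 11% to 49% of counted cases, for an assumed q of 0.25% to 2%. At the low end this is minor; at 1% or more it would affect interpretation.

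Two further inferences are not supported. The sample size is not wrong: 492 reproduces and does not change. Nor should dual positivity simply become the primary event: under the assumptions in step 5 it keeps about 2.6 of 3.3 carried-over infections and loses about 2.9 of 7.9 true ones.

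**What to change.** Keep the post-travel diagnosis as the outcome, and classify each case by test pattern once the section 2.5 repeats are complete:

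- TST conversion from a documented negative baseline TST, with or without a positive QFT-Plus;
- QFT-Plus conversion, where a negative baseline QFT-Plus exists;
- TST-negative/QFT-Plus-positive with no baseline QFT-Plus: *infection, timing unknown*.

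Report the incidence rate and the risk-factor model with and without the third class, and state in the limitations that the test sets before and after travel differ. Reconcile the abstract with section 2.3 on who is retained after a positive baseline TST.

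The cost is outcome wording and one added analysis, with no extra test and no larger sample. The rate is less precise when the third class is left out, and some true new infections leave that version of the count. Infections missed by the baseline TST that are TST-positive later are not removed and should be stated as a remaining limitation. This concerns outcome classification only, not care.

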### Outcomes

2.4

#### Primary outcome

2.4.1

The primary outcome is the diagnosis of LTBI and/or TB after travelling to a high TB incidence country in accordance with World Health Organization (WHO) guidelines.^[1]^ At the end of the study, patients will be classified as: “not infected; LTBI/TB disease; unknown/lost to follow-up”. Table 2 shows study variables and timing of data collection.

**Table 2 T3:**
[figure not shown]
Study variables and timing of data collection.

#### Secondary outcomes

2.4.2

1.Sociodemographic data: sex, age, country of birth, country of birth of mother and father.2.Clinical data: weight and height (before and after travel), BCG vaccination, presence of BCG scar.3.Epidemiological data: pre-travel visit date, travel date, post-travel visit date, return date of the travel, trip duration, travel country, number of people that lived in host home, travel environment (rural / urban / mixed), smokers in host home, contact with a person suspected of having TB.

### TST and QFT-Plus test procedures

2.5

Tuberculin Skin Test (TST): TST will be performed by intradermal injection of 2 UT of PPD RT23 (Statens Serum Institut, Copenhagen, Denmark) and read after 48 to 72 hours. A positive test is defined as an induration greater than or equal to 10 mm according to recommendations from the *Agència de Salut Pública de Catalunya*^[23]^ and WHO guidelines.^[1]^

QuantiFERON-TB Plus (QFT-Plus) (Cellestis, Victoria, Australia; QIAGEN, Dusseldorf, Germany): We will draw four ml of blood per child and interpret the QFT-Plus test according to manufacturer's instructions. Values ≥ 0.35 IU/ml in either TB1 and/or TB2 antigen tubes will be considered positive.^[24]^ In the case of QFT-Plus values ≥0.2 and <0.35 (gray zone), the test will be repeated 4 to 8 weeks later. QFT-Plus can have a positive, negative or indeterminate result.

If TST and QFT-Plus results are discordant, the test with a negative result will be repeated 4 to 8 weeks later.

### Statistical analysis

2.6

Qualitative variables will be described using frequency tables, and quantitative variables will be determined using median, mean and interquartile range (IQR). We will use paired proportions for comparisons. The incidence rate of LTBI and TB will be estimated per individual/month and person/year per country visited and by age group. To identify factors associated with presence of LTBI or TB, the Fisher exact test or Chi-square test and the Mann-Whitney test will be used for bivariate analyses, followed by analysis of logistic regression calculating odds ratios and 95% confidence intervals. A 5% type I error will be estimated. Data will be exported from the REDCap database to PASW Statistics 25 (SPSS Inc., Chicago, IL) for statistical analyses.

### Ethics

2.7

This study protocol (version 2, 01/02/2016) has been approved by the Clinical Research Ethics Committee of the *Hospital Universitari Mútua Terrassa* on 24/02/2016 (code 02/16) and by the Clinical Research Ethics Committee of the *Fundació Institut Universitari per a la recerca a l’Atenció Primària de Salut Jordi Gol i Gurina* (IDIAPJGol) on 25/04/2016 (code P16/094), in agreement with the Declaration of Helsinki/Tokyo. All parents or legal guardians of the participants will receive oral and written information about the study and Informed Consent will be obtained. Any amendment to the study protocol will be submitted to the ethical committees for approval.

The REDCap© database will be exclusively used by the team of researchers. The data included in the database used for statistical analyses will be anonymized and identified with internal codes of the project to avoid identification by the investigative team to guarantee confidentiality.

The results of the study will be published in scientific journals and will be presented in national and international meetings. The results will be communicated to participants in a meeting and via local and national media, and will also be disseminated to the general population.

## Discussion

3

This study aims to evaluate the risk of LTBI and TB in paediatric VFR travellers that live in Catalonia, a low incidence TB region.^[20]^ The study will be conducted in primary care centres, specialized travel clinics and hospital paediatric departments of the public health-care system. The joint role of primary care and infectious disease specialists is crucial in the implementation of strategies aimed at the eradication of TB in this population.^[25]^ To our knowledge, this is the first study to prospectively analyse collected data from VFR children.

The few studies published with adults to date suggest that in non-VFR travellers, the risk of infection is similar to the local annual risk of TB infection.^[26]^ In contrast, studies conducted with the immigrant population suggest that a significant percentage of TB cases are related to recent travel to the country of origin.^[27]^ In the case of children, a population group with higher susceptibility to develop TB after primary infection, a case-control study from California reported an increased risk of LTBI in young paediatric VFR travellers and children of families that hosted visitors from countries with high TB incidence.^[28]^

Awareness of travel-associated risk of disease in VFR remains low, which might explain the scarce use of pre-travel health-care services by the immigrant population.^[29]^ Moreover, the diversity of recommendations for different regions and countries demonstrates the limited information available on this topic.^[30,31]^ Knowledge about the effectiveness of LTBI screening or BCG vaccination strategies also remains poor.^[32]^ The implementation of strategies for the detection and treatment of LTBI cases should be prioritized to prevent new cases of TB in the paediatric and the adult population.^[33]^

Since state-level data are those usually published in official reports and regional incidence could vary significantly within the same country, a limitation of the study is the unavailability of data on regional incidence, which may hinder the assessment on the intensity of exposure to *M tuberculosis*.^[17]^ In addition, due to the specific immigration patterns of Catalonia, some countries of origin will be overrepresented in our sample.

The lack of gold standard for LTBI diagnosis responds to its paucibacillary nature, the quiescent state of *M tuberculosis* and the localization in the mediastinal lymph nodes.^[34]^ However, this is a universal limitation in all studies on this issue.

The low positive predictive value of the screening tests of LTBI in the general population constitutes another limitation. However, in low burden countries and among high risk groups such as immigrants and VFR travellers, tests may be useful for LTBI screening.^[35]^

Similarly, the TST and interferon-γ release assays have well described limitations, which can hinder the interpretation of results and the calculation of incidence rates, especially in the case of discordant results.^[36,37]^ Again, this is a universal limitation in all studies on this issue.

The study will implement and evaluate a new detection strategy and management of LTBI in VFR children in a country with a low incidence of TB. This strategy may prove useful to design public health policies in regions with low incidence of TB with significant numbers of VFR travellers.
